### Participants

A total of 50 GPs from 50 offices at 32 primary care centers of the Spanish National Health System are participating in the Dislip-EM study
[19]. The following subpopulations are being studied:

-Subpopulation 1: To test the expert-expert, evaluator-evaluator intraobserver reliability, and the expert-evaluator interobserver reliability, a sample of 18 interviews with standardized patients will be performed (eight of which will be EG patients -where GPs are expected to perform MI-, and another eight with CG patients -where GPs are not expected to perform MI). The purpose of using two subsamples is to ensure the collection of different levels of performance concerning the model that the instrument must record and discriminate. The interviews will be selected at random from the 162 that have already been performed with simulated patients.

-Subpopulation 2: For the purposes of this study, each GP will recruit eight-nine regular patients. Each clinician is expected to video record their encounters with a patient selected randomly, in their visits at 2, 4, 8 and 12 months so, at the completion of this stage, 200 interviews will be available in video format. The analysis of the different types of validity (content, construct, sensitivity to change) will be performed by using the samples from both subpopulations (n=162 from the simulated interviews plus 200 from real interviews, making a total of 362 interviews). The assessment of such interviews by the EVEM tool will be conducted by one of the expert physicians.

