**Methods/Design:**

The hypothesis of this study is that the Scale for Measuring Motivational Interviewing Skills (EVEM questionnaire) is a valid and reliable instrument for measuring the primary care professionals skills to get behavior change in patients. To test the hypothesis we have designed a prospective, observational, multi-center study to validate a measuring instrument. –Scope: Thirty-two primary care centers in Spain. -Sampling and Size: a) face and consensual validity: A group composed of 15 experts in Motivational Interviewing. b) Assessment of the psychometric properties of the scale; 50 physician- patient encounters will be videoed; a total of 162 interviews will be conducted with six standardized patients, and another 200 interviews will be conducted with 50 real patients (n=362). Four physicians will be specially trained to assess 30 interviews randomly selected to test the scale reproducibility. -Measurements for to test the hypothesis: a) Face validity: development of a draft questionnaire based on a theoretical model, by using Delphi-type methodology with experts. b) Scale psychometric properties: intraobservers will evaluate video recorded interviews: content-scalability validity (Exploratory Factor Analysis), internal consistency (Cronbach alpha), intra-/inter-observer reliability (Kappa index, intraclass correlation coefficient, Bland & Altman methodology), generalizability, construct validity and sensitivity to change (Pearson product–moment correlation coefficient).

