## Methods

The conceptual hypothesis has formulated so: “Is the Scale for Measuring Motivational Interviewing Skills (EVEM, acronym in Spanish of “Escala de Valoración de la Entrevista Motivacional”) a valid and reliable instrument to measure the skills of primary care professionals ?”.

The main objective of this study, therefore, is to validate the EVEM questionnaire for its use in clinical interviewing with patients suffering from dyslipidemia.

The specific objectives are:

1. Developing a scale and assess its qualitative validity;

1.a) Developing and identifying scale items -basing on the theoretical model- and preparing a draft questionnaire for assessing general practitioners’ motivational interviewing skills;

1.b) Conducting an assessment based on expert opinions: face, consensual and content validity;

2. Analyzing the psychometric properties and attributes of the scale:

2.a) Assessing the questionnaire’s validity and reliability:

2.a.1.-in terms of reproducibility and variability (inter-observer reliability, intra-observer agreement -test-retest);

2.a.2.-in terms of homogeneity (scale internal consistency);

2.b) Assessing the generalizability of EVEM reliability;

2.c) Assessing its dimensionality (factor analysis);

2.d) Refining the scale contents (response rate, item-total correlation, reliability).

2.e) Assessing the scale’s sensitivity to change.

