### Action plan

The procedure in each stage is as follows:

-Stage 1: design of a questionnaire (Objective 1.a). The scale is designed in consistency with the underlying theoretical model, with the analysis of the scientific literature available, and with scientific evidence on clinical communication
[3,5,6,20].

-Stage 2: qualitative validation (objective 1.b). To analyze the face and consensual validity of the questionnaire, a group of 15 key-informants specially trained in clinical communication was created. Then, Delphi-type methodologies were implemented in an iterative process of three e-mail rounds
[21]. Once this stage was completed, three versions were obtained from the first EVEM version (see Additional file
1). Further, a manual was prepared for the evaluator in two formats: an extended version and an abridged version.

-Stage 3: psychometric properties and attributes of the scale (Objective 2): Objective 2.a): intra-/inter-observer agreement/reliability:

2.a.1. Intraobserver reliability: four evaluators (two experts and another two non-experts in MI -previously trained in the use of EVEM- will assess twice, separately and independently the same sample of 18 interviews randomly selected –from the 162 interviews done with standardized patients- in a 4–6 week interval. Evaluators are general practitioners with clinical experience and advanced theoretical/practical knowledge on MI.

2.a.2. Interobserver reliability: for training purposes, expert raters will invite non-expert to watch motivational interviewing videos of different models (stages of change) and quality, for providing feedback to the EVEM scale. Both non-expert observers and the two experts will independently assess the 18 interviews to assess interobserver agreement.

2.b) Concomitantly, the reliability-generalizability coefficients will be estimated. Considering the results obtained by our research group in the validation process of a questionnaire for assessing patient-centered interviews, such coefficients are expected to be between six and nine interviews
[13].

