## Statistical analysis

### Stage 2: qualitative analysis (objective 1.b)

In the third Delphi round, the relevance/value of the questionnaire items was weighted by using a five-degree ordinal score scale. From the results obtained, the arithmetic mean, mode, distribution intervals and variance of each item were estimated as a way to measure the level of agreement. Therefore, high variance would represent a low level of agreement on the relevance of each item, and vice versa.

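### Content validity is assigned to the experts in objective 1.b but to factor analysis and the recorded interviews elsewhere; interview data cannot show it, and the experts' relevance ratings are read only as agreement

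*Protocol article*

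**What the plan says.** The protocol article places content validity in different hands in different sections.

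- **Methods, objective 1.b** gives it to the experts: "Conducting an assessment based on expert opinions: face, consensual and content validity".
- **Abstract, Methods/Design** gives the 15 experts face and consensual validity. Among the properties evaluated on the video-recorded interviews it lists "content-scalability validity (Exploratory Factor Analysis".
- **Action plan, Stage 2**, which carries out objective 1.b, drops content validity from the experts' task: "To analyze the face and consensual validity of the questionnaire, a group of 15 key-informants specially trained in clinical communication was created".
- **Participants, Subpopulation 2** assigns it to the interviews: "The analysis of the different types of validity (content, construct, sensitivity to change) will be performed by using the samples from both subpopulations", with the sample given as "n=162 from the simulated interviews plus 200 from real interviews, making a total of 362 interviews".
- **Statistical analysis, Stage 2** reports that in the third Delphi round "the relevance/value of the questionnaire items was weighted by using a five-degree ordinal score scale". The mean, mode, distribution intervals and variance of each item were computed, all introduced as a way of gauging agreement. The one interpretation offered is that "high variance would represent a low level of agreement on the relevance of each item", and the reverse for low variance.
- **Statistical analysis, Stage 3**, and objective 2.c, use factor analysis for dimensionality and do not mention content validity there.

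**The concern.** Content validity asks two things: is each item relevant to the construct, and do the items together cover it? Both are judgements about items against a definition of motivational interviewing. Factor analysis starts from the items already chosen and describes how their scores covary. An irrelevant item that correlates with the others will load, and a skill that was never written into the scale leaves no trace in the correlation matrix.

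The study's hypothesis is that EVEM is valid and reliable. If the Abstract and Participants are followed as written, a clean factor solution could be offered as support for content validity. The expert ratings, which do speak to relevance, would then be reported as consensus alone.

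**Working it through.** **1. The plan's own figure.** 50 GPs × 4 visits (2, 4, 8 and 12 months) = 200 real interviews; 162 + 200 = 362. The stated total reproduces exactly and is not in dispute.

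**2. The assignments side by side.**

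| Section | Evidence for content validity |
|---|---|
| Methods, objective 1.b | Expert opinion |
| Abstract, Methods/Design | Exploratory factor analysis |
| Action plan, Stage 2 | Not named for the experts (face and consensual only) |
| Participants, Subpopulation 2 | 362 recorded interviews |
| Statistical analysis, Stage 3 | Not named; factor analysis is for dimensionality |

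The first row cannot be reconciled with the second and fourth. The third leaves the expert stage without the task that objective 1.b gives it.

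**3. Can factor analysis reveal missing content?** A single simulated data set (one seed) illustrates the point. From the protocol: n = 362, 16 items, three answer categories. Assumed: three independent domains, loadings of 0.7, cut points at ±0.5 SD. One version covers all three domains (6 + 5 + 5 items); the other omits one domain (8 + 8 items).

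| | KMO | Bartlett χ² | Eigenvalues > 1 | Cronbach's α |
|---|---|---|---|---|
| Three domains covered | 0.79 | 1399 | 3 | 0.68 |
| One domain omitted | 0.89 | 1693 | 2 | 0.77 |

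The incomplete scale looks no worse; KMO and α are higher because each remaining domain has more items. Nothing in the output signals that a domain is absent. The values depend on the assumptions, but the reason does not: absent items contribute no correlations.

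**4. What the expert summaries can show.** Hypothetical sets of 15 ratings on a 1–5 scale, with variance s² = Σ(x − x̄)²/(n − 1):

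- Eight 4s and seven 5s: mean (32 + 35)/15 = 4.47, mode 4, variance 0.267.
- Eight 2s and seven 1s: mean (16 + 7)/15 = 1.53, mode 2, variance 0.267.

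Variance, the only summary the plan interprets, does not separate the two items. The mean and mode do, and the plan computes both. The information on relevance therefore exists but is not read as such.

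**5. Precision if relevance is expressed as a proportion.** Exact (Clopper–Pearson) limits solve P(X ≥ x | L) = 0.025 and P(X ≤ x | U) = 0.025 with n = 15.

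- Assumed 12/15 = 0.80: 95% CI 0.519 to 0.957.
- Assumed 15/15 = 1.00: lower limit 0.025^(1/15) = 0.782.

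The counts are assumptions; the article reports no ratings.

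**The case against.** The best defence is that this is loose labelling. The operative analysis text uses factor analysis for dimensionality, and only a phrase in the Abstract links it to content. The Participants sentence does not name factor analysis, and its reference to content could mean objective 2.d, refining the scale by response rate and item-total correlation, which does need interview data. Items were also built from a theoretical model and the literature and revised over three Delphi rounds, which bears on coverage. The expert stage is complete and no Stage 3 computation would change.

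Much of this stands, and it rules out three stronger readings that a reader might infer:

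- *The experts' ratings are summarised by variance alone, leaving objective 1.b with no usable statistic.* Not so: the mean, mode and distribution intervals are computed too.
- *Content validity rests solely on the wrong evidence.* Not so: objective 1.b names the experts, and item development is described.
- *The lack of a content-validity index or relevance cut-off is itself an error.* A journal article may leave that to the full protocol. Such an index would not reveal missing skills either.

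The contradiction remains. The Participants sentence lists content as a type of validity, beside construct validity and sensitivity to change, so the item-refinement reading is strained. The Abstract ties the property to a named method. Condensation explains an omission, but it does not explain giving one property to two different sources of evidence.

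**Conclusion.** The point holds as an internal contradiction with a consequence for interpretation. Content validity is given to the experts in one place and to interview data or factor analysis in two others, and the section that implements the expert stage does not name it. Followed as written in the Abstract and Participants, item covariance would be offered for a property it cannot show. The expert ratings are presented only as agreement, although the computed summaries also carry relevance.

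The size is limited: no sample size, error rate or data collection is affected. What changes is which evidence may support a statement on content validity. The conclusion rests on the usual meaning of the term (relevance and coverage of items). It does not depend on the simulation settings or on the assumed rating counts.

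**What to change.** 1. In the Abstract and in Participants, remove content validity from the interview-based analyses. Call the factor analysis structural (construct) validity, in line with its stated use for dimensionality.
2. In the Action plan, Stage 2, name content validity as a task of the expert stage, to agree with objective 1.b.
3. In Statistical analysis, Stage 2, read the location of the existing third-round ratings as evidence of relevance: the mean, the mode, or the share of the 15 experts rating an item relevant, with an exact 95% CI. Any cut-off should be justified from the anchors of the rating scale, which the article does not give. Keep variance as the measure of consensus. A formal content-validity index is optional.
4. Draw any statement on coverage from the item-development work and the Delphi rounds, since ratings of existing items cannot show what is missing.

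The cost is a short re-reading of ratings already in hand and wording changes in four places; no new data are needed. The downside is that intervals from 15 experts are wide, and some items may show only modest relevance.

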### Sample size

The sampling unit is the video recording of a clinical interview. From a general approach, most of authors agree that, in questionnaire validation studies, a sample size of 200–300 or 5–10 participants (in this case, clinical interviews) per scale variable would be adequate
[22,27,29]. Thus, considering that the last version of the scale has 16 items, the number of interviews required would be 80–160.

To calculate the sample size required to estimate inter-/intra-observer agreement, the formula developed by Norman & Streiner
[30] was used. They establish that the desirable minimum sample size can be estimated by the formula n= 2 x C^2^, where C is the number of answer categories. As the scale has three answer categories, the desirable minimum sample size is 18 interviews.

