### Study design

For testing our hypothesis we used two epidemiological designs: A qualitative study in its first stage (expert opinions, Delphi technique), and a quantitative, prospective, observational and multicenter study in its second stage. Figure
1 shows the study protocol design. This study approaches the complementary objective of the Dislip-EM project, a cluster randomized, controlled clinical trial designed to assess the effectiveness of Motivational Interviewing in reducing cardiovascular risk and improving lipid control in patients with hyperlipidemia
[19].

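### Interviews are taken as the unit although they are repeated within 50 GPs, so an interview-level comparison of intervention and control GPs would overstate precision

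*Protocol article*

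**What the plan says.** All references are to the protocol article.

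- **Sample size.** "The sampling unit is the video recording of a clinical interview". Interviews stand in for participants in a rule of 5 to 10 per item (200–300 is given as an alternative), so with 16 items "the number of interviews required would be 80–160".
- **Participants.** "A total of 50 GPs from 50 offices at 32 primary care centers of the Spanish National Health System are participating". Each GP films one randomly chosen patient "in their visits at 2, 4, 8 and 12 months", which gives 200 real interviews. Content validity, construct validity and sensitivity to change use "n=162 from the simulated interviews plus 200 from real interviews, making a total of 362 interviews".
- **Statistical analysis, Stage 3.** Construct validity compares the two randomised groups of the parent trial, with n=110 in each. Sensitivity to change has two parts. The first compares mean scores between intervention and control GPs, and before with after training within the intervention group, using the 162 standardized-patient interviews. The second is a Pearson correlation with 12-month patient outcomes, judged at p ≤ 0.05.
- **Study design.** The parent study is "a cluster randomized, controlled clinical trial".

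The article does not mention clustering by GP, a design effect, aggregation to the GP or a model with a GP effect.

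**The concern.** EVEM is meant to measure a professional's skill, so two interviews by the same GP should score more alike than interviews by different GPs. The article relies on this itself. Under Protection against bias it argues that clinicians rarely alter how they interview, and Stage 3 plans a generalizability step based on an ICC.

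Training is allocated to GPs or to larger clusters; the article does not say which level was randomised. A contrast between arms is therefore a contrast between GPs, and extra interviews by the same GP add less information than interviews by new GPs. An analysis that counts each video as a separate unit gives a standard error that is too small. The between-arm difference and the link to patient outcomes are main parts of the planned evidence for construct validity and sensitivity to change, so false-positive findings there would bear directly on the study hypothesis.

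**Working it through.** **The plan's own figures.** 16 × 5 = 80 and 16 × 10 = 160; 50 × 4 = 200; 162 + 200 = 362. All reproduce. The arithmetic is right; the question is the unit.

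**Inputs.** From the article: 50 GPs, 200 real interviews (4 per GP), 362 in total (362/50 = 7.24 per GP on average), 162 simulated interviews. Assumed: 25 GPs per arm, two-sided tests, and a GP-level ICC (ρ), which the article does not give. I use 0.1, 0.3 and 0.5. As a plausibility check, Action plan expects six to nine interviews to be needed for generalizability but gives no target coefficient G. If G is 0.80 to 0.856, Spearman-Brown inverted, ρ = G/(k − G(k−1)), gives 0.31 (k = 9, G = 0.80) to 0.50 (k = 6, G = 0.856).

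**Between-arm test.** The design effect for a mean is DE = 1 + (m−1)ρ. A naive two-sided 5% test has true error 2[1 − Φ(1.96/√DE)].

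| ρ | DE, m = 4 | Error (formula) | Error (simulated) | DE, m = 2.2 | Error (formula) |
|---|---|---|---|---|---|
| 0.1 | 1.30 | 0.086 | 0.083 | 1.12 | 0.06 |
| 0.3 | 1.90 | 0.155 | 0.152 | 1.36 | 0.09 |
| 0.5 | 2.50 | 0.215 | 0.223 | 1.60 | 0.12 |

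The m = 4 columns describe the 200 real interviews. In simulation, a t-test on GP means returned 0.051 and 0.049 at ρ = 0.3 and 0.5. The m = 2.2 columns describe the simulated interviews if the 162 split evenly over three cells (intervention before, intervention after, control): 162/3 = 54, and 54/25 ≈ 2.2 per GP per cell. If the 110 per group are interviews, m = 110/25 = 4.4 and the formula gives 0.17 at ρ = 0.3 and 0.23 at ρ = 0.5.

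**Correlation with 12-month outcomes.** One patient per GP is filmed, so there are at most 50 independent patient/GP pairs. With r = t/√(n−2+t²), the critical |r| at two-sided 0.05 is 0.279 for n = 50 and would be 0.139 if 200 rows were used. Simulated error with 200 rows is 0.082, 0.161 and 0.215 at ρ = 0.1, 0.31 and 0.5. With one mean per GP it is 0.047 to 0.050.

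**Before/after within the intervention group.** The same GPs appear in both periods, so a stable GP effect cancels from the difference. The true variance is (1−ρ) times what an unpaired test assumes, and the error is 2[1 − Φ(1.96/√(1−ρ))]: 0.019 at ρ = 0.3 and 0.006 at ρ = 0.5. The unpaired test is conservative. This takes the GP effect to be the same in both periods.

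**Factor analysis, alpha and item-total correlations.** These use covariances, for which the inflation is about 1 + (m−1)ρ² (normal data, same ICC for all items). With m = 7.24 the factor is 1 + 6.24ρ², that is 1.25, 1.56, 2.56 and 4.06 at ρ = 0.2, 0.3, 0.5 and 0.7. Dividing 362 by these gives an effective n of about 290, 232, 141 and 89.

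**The case against.** The strongest reply is that the article never says interviews are independent and does not name a test for the between-arm contrast. Student's t appears only for paired observer scores. The training comparison speaks of scores obtained by professionals, which could be GP-level. A condensed article may leave a mixed model to the full protocol or analysis plan, and no document gives a within-GP ICC.

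Part of this stands. The error rates above describe what an interview-level test would do, not a test the article commits to, and their size depends on an assumed ICC and arm split. The row count for the Pearson test is also unstated. A reader might infer that 200 or 362 rows will be used, but the text does not say so, and a patient-level pairing with n = 50 fits it equally well. The number of GPs behind the 162 simulated interviews is not given separately either.

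The reply does not remove the point, because the article does more than stay silent. It fixes the interview as the sampling unit, pools 362 interviews for these validity analyses, and sets 110 per group for construct validity. Since 2 × 110 = 220 exceeds 50, that unit lies below the GP, whatever it is; it matches neither 200 nor 362.

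Two stronger readings are tempting, and neither is supported. One is that every standard error, including the before/after one, is too small; for that contrast the sign is reversed. The other is that the factor-analysis sample fails the plan's rule. That would follow only from applying the design effect for means to covariances. Agreement between raters on the 18 interviews is little affected.

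**Conclusion.** The concern holds for inference between GPs. The article sets the unit at or near the interview where the independent information comes from 50 GPs. An interview-level between-arm test at nominal 5% would have a true error of about 9%, 15% and 22% at ICC 0.1, 0.3 and 0.5 for four interviews per GP, and about 6%, 9% and 12% for about 2.2 per GP per cell. The outcome correlations carry at most 50 independent pairs. These sizes rest on the assumed ICC, 25 GPs per arm and equal numbers per GP.

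For the before/after contrast the consequence is lost power, not false significance. For the factor analysis, 362 overstates the information, but the effective n stays above the plan's lower bound of 80 up to an ICC of 0.7. Inadequacy is therefore not shown.

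**What to change.** - State that interviews are nested within patients and GPs, and that the GP is the unit of inference for between-arm contrasts. Analyse these on GP means or with a mixed model that has a GP random intercept.
- Analyse before and after training as paired within GP.
- Correlate 12-month outcomes with one mean EVEM score per filmed patient/GP (n = 50).
- Obtain intervals for alpha, item-total correlations and factor loadings by bootstrapping GPs.
- Restate the sample as 362 interviews from 50 GPs, and say what the 110 per group counts.

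No new data are needed. The cost is a change of wording and analysis, wider confidence intervals and a less favourable stated sample. The paired before/after analysis should gain power.
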